## Introduction

### Background

Maternal weight gain in pregnancy is necessary for healthy fetal development [1]. The Institute of Medicine [1] recommends that appropriate weight gain for normal weight women is 25-35 pounds, whereas weight gain for overweight (15-25 pounds) and obese (11-20 pounds) women is less; any weight above these upper guidelines is considered excessive or high. High gestational weight gain (GWG) is strongly related to and independently predicts adverse pregnancy outcomes (eg, preterm delivery, gestational diabetes, and pre-eclampsia), greater adiposity, postpartum weight retention, and long-term obesity and cardiovascular disease [1,2]. Maternal obesity and high GWG also elevate infant risks such as macrosomia and early onset of obesity and diabetes [1]. As GWG is a modifiable factor that can be targeted to reduce adverse risks, managing GWG is critical for the mother, and can influence the etiology of obesity for offspring at a crucial time in the life cycle. However, over 50% of women enter pregnancy as already overweight (body mass index, BMI, 25-29.9 kg/m^2^) or obese (BMI ≥30 kg/m^2^) [3], and nearly 60% of women with overweight/obesity gain more weight in pregnancy than that recommended by the Institute of Medicine [1], which suggests they have particular challenges with managing their weight.

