**Figure 1 figure1:**
[figure not shown]
Flow of participants through Healthy Mom Zone Intervention (still underway) as per Consolidated Standards for Reporting Trials guidelines. Participants allocated to intervention group could be assigned to various step-ups throughout the intervention time period. Step-ups will vary by individual and time-point of intervention and gestation. Incomplete cells are due to ongoing data collection.

**Table 1 table1:** Healthy Mom Zone measurement protocol. X designates when the measurement had taken place. All participants completed this measurement protocol.

Variable	Assessment	Time point						
		Pr^a^	Po^b^	D^c^	W^d^	BiW^e^	M^f^	Pp^g^
Weight and weight gain	High Precision Stand-On Adult Scale	X	X					X
	FitBit Aria Wi-Fi Smart Scale			X				X
Height	Stadiometer	X						
Serum blood	Macronutrients	X	X					
Adiposity	Air-Displacement Plethysmography (BODPOD) Body Composition	X	X					X
Healthy eating behaviors	MyFitnessPal Phone App				X			
	3-Factor Eating Questionnaire	X	X				X	
	Remote food photography		X					X
Physical activity behaviors	Actigraph (time spend in moderate-intensity activity)	X	X				X	
	Jawbone Wrist-Worn Activity Monitor	X	X	X				X
	Physical activity log (mode and min activity)							X
	Leisure-Time Exercise Questionnaire	X	X				X	
Weight attitude	Palmer attitudes toward weight in pregnancy	X	X				X	
Healthy eating and exercise motivational determinants	Attitude, subjective norm, perceived control, intention	X	X				X	
	Healthy eating and exercise beliefs	X	X		X			
Self-regulation	Self-regulation index	X	X			X		
	Self-Regulation Questionnaire (self-regulatory function)	X	X			X		
	Self-control scale	X	X				X	
Sociodemographic	Health history Questionnaire	X						
	Pregnancy complications	X			X			
Self-efficacy	Sui Healthy Eating and Physical Activity Self-Efficacy Scales	X	X				X	
	Clark Weight Efficacy Scale	X	X				X	
Sleep behaviors	Pittsburgh Sleep Quality Index	X	X				X	
	Jawbone Wrist-Worn Activity Monitor	X	X	X				X
Psychosocial	Center for Epidemiological Studies Depression Scale	X	X				X	
	State Trait Anxiety Inventory	X	X			X	X	
	Body Areas Satisfaction Scale	X	X				X	
	Perceived Stress Scale	X	X		X			
	Pregnancy Figure Rating Scale	X	X				X	
	Rothbart Adult Temperament Scale	X						
Stress	Urine cortisol collection	X	X		X			X
Metabolism	Breezing device	X	X		X			X
Fetal Growth	Standard fetal ultrasound scans						X	

^a^Pr: preintervention.

^b^Po: postintervention.

^c^D: daily.

^d^W: weekly.

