### Participants and Sample Size

The target sample for this intervention is 30 pregnant women with overweight and obesity (BMI range 25-45 kg/m^2^; >40 kg/m^2^ with physician consultation); singleton pregnancy >8 weeks gestation; English-speaking; residing in or near Centre County, Pennsylvania; and with physician consent to participate. On the basis of our past research [27,28], this group compromises >85% of live births in Central Pennsylvania. Exclusion criteria are multiple gestation, diabetes at study entry, not overweight or obese, severe allergies or dietary restrictions, contraindications to prenatal physical activity [29], and not residing in area for duration of the study. The primary outcome of our study is GWG. Julious [30] effectively argues a sample size of 12 per group is adequate to assess feasibility and obtain sufficient precision of the mean and variance to perform a formal sample size and power calculation for a future larger randomized control trial with GWG as the primary outcome. With 24 participants (12 per group), we will have 80% statistical power to detect a standardized effect size (difference between 2 group means divided by SD) for GWG of 1.2 using a 2-sided test with significance level of *P*=.05. Factoring in participant dropout (conservative estimate of 25% based on our pilot work [31,32] and past research [5]), we will recruit 30 participants (15 intervention, 15 control).

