### Recruitment, Assignment, and Allocation

Women are recruited using on-site clinic, community-based, and Web-based strategies. At the clinic, nurses identify potential eligible women and refer them to a study staff member who is ready in the waiting room to speak with them about the study and, if interested, screen them for eligibility. Community-based recruitment includes hanging study flyers at local businesses, churches, campus, and community centers. Web-based recruitment occurs through the study website [33] and Facebook ads. Interested women call a toll-free number. A project staff member explains the study, obtains verbal assent to ask questions, and determines eligibility based on the inclusion criteria described above. Pregnant women with overweight and obesity are recruited between 8 and 12 weeks gestation and randomized to the intervention or control condition until about 36 weeks gestation. The study biostatisticians developed a randomization scheme using variable size, random permuted blocks to ensure the number of participants in each group is balanced after each set of *B* randomized participants, where *B* is the block size. Randomization to intervention (n=15) or control (n=15) groups uses 1:1 allocation; participants are entered consecutively. When a woman is eligible and informed consent is signed, a staff member requests randomization by a unique participant identification number.

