### Decision Rules and Adapting the Intervention Dosage

A set of decision rules were developed to evaluate GWG that are based on the Institute of Medicine GWG guidelines (ie, overweight=15-25 pounds; obese=11-20 pounds) [1], our own research [36,37,50], and clinical insight that inform when and how to adapt the components. A computerized applet is used to plot women’s weight against individual weight gain trajectories with lower and upper bounds for the GWG guidelines [52,53]; GWG is evaluated weekly and the values are compared with average weekly weight ranges for overweight (eg, 0.5-0.7 pounds) and obese (eg, 0.4-0.6 pounds) women [1]; these weekly weights are then evaluated in 3-4 week cycles to determine if and when the intervention dosage should be adapted (see Multimedia Appendix 2). The rationale for adapting the dosages is based on each woman’s self-regulatory abilities to manage GWG. For example, if the woman is within her GWG goal (ie, weekly weight gain ranges according to the Institute of Medicine guidelines) [1], she will continue to receive the same level of the intervention for the next cycle as she is adequately self-regulating her weight with the amount of intervention dosage that she’s receiving. However, if she is exceeding her GWG goal, the intervention is adapted (ie, dosage is stepped up). That is, she continues to receive the baseline intervention, but then she receives additional active learning components (eg, step-up 1 with cooking and grocery store demonstrations; onsite exercise session led by an instructor) to help better self-regulate her weight. If she exceeds her GWG goal at the next evaluation cycle, the intervention will be adapted again (ie, baseline + step-up 1 + step-up 2) with other active learning components (eg, portion size and containers; second onsite exercise session with instructor) added to provide more intensive intervention assistance and supportive control to better manage GWG. This evaluation process continues over the course of her pregnancy until the end of the intervention (ie, around 36 weeks gestation) and/or a maximum of 5 possible dosage increases (see Multimedia Appendix 3). The sequencing of the adaptive dosages was determined during pilot testing by examining combinations of active learning strategies with good user acceptability, and we identified the maximum number of dosage increases that resulted in “too much intervention burden” and led to participant dropout (ie, more than 5 adaptations) [50]. If a participant is under her GWG goal [1] and/or any safety concerns emerge (eg, complication such as anemia, fetal issue), we consult with the study obstetrician who makes recommendations on if and/or how intervention dosage changes should be made.

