### Data Analysis

To establish initial validation of the intervention, contrasts constructed from linear mixed-effects models [54] will be used to assess differences between the intervention and control groups with respect to changes in continuous outcomes over time (from pre- to postintervention): changes in primary (GWG, energy intake, physical activity, planned/self-regulatory behaviors) and secondary outcomes (serum blood biomarkers, adiposity, knowledge). Linear mixed-effects models are an extension of ordinary regression models that account for within-subject variability inherent in longitudinal studies. Generalized estimating equations [55] with a logit link will be used to assess differences between the intervention and control groups with respect to dichotomous outcomes over time. If deemed necessary, confounding variables (eg, prepregnancy weight, age, obstetric complications) will be included as covariates. With respect to the participants meeting individual GWG goals based on prepregnancy BMI status [1], we will look at each woman and determine whether she met her GWG goal. We will code participants as “0” for GWG within goal, +1 for GWG over goal, and −1 for GWG under goal. A chi-square test will be used to assess differences between the intervention and control groups on this 3-level ordinal variable (ie, −1,0,1) assessing individual GWG goals. All hypothesis tests will be 2-sided, and analyses will be performed using SAS software version 9.4 (SAS Institute Inc., Cary, NC) or R software (R Foundation for Statistical Computing, Vienna, Austria).

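### Obstetric complications are listed as a possible confounder without being limited to values before randomisation, so adjusting for them can pull the GWG contrast toward zero

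*Protocol article*

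**What the plan says.** The Participants and Sample Size section states: "The primary outcome of our study is GWG". The Data Analysis section compares the arms by contrasts from linear mixed-effects models for change from pre- to postintervention, and by generalized estimating equations for dichotomous outcomes. It then adds: "If deemed necessary, confounding variables (eg, prepregnancy weight, age, obstetric complications) will be included as covariates". It does not say at what time the complications variable is to be taken.

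Other parts of the article bear on what that variable is:

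- Table 1 has a row "Pregnancy complications" with a mark in the preintervention column and another in the weekly column.
- Women are "recruited between 8 and 12 weeks gestation and randomized to the intervention or control condition until about 36 weeks gestation" (Recruitment, Assignment, and Allocation).
- "Exclusion criteria are multiple gestation, diabetes at study entry" (Participants and Sample Size), so gestational diabetes as a complication would be expected to appear after entry.
- The section on decision rules provides for the case that "any safety concerns emerge (eg, complication such as anemia, fetal issue" during the intervention.
- The Background says: "High gestational weight gain (GWG) is strongly related to and independently predicts adverse pregnancy outcomes (eg, preterm delivery, gestational diabetes, and pre-eclampsia". It goes on: "As GWG is a modifiable factor that can be targeted to reduce adverse risks".

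**The concern.** A confounder of a treatment comparison is related to how treatment was assigned. Randomisation removes that relation in expectation for everything fixed at baseline. Something that happens afterwards cannot have influenced the assignment, so a complication arising in follow-up is not a confounder of the arm contrast.

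The article's own rationale also places such complications after weight gain. GWG is said to predict them, and GWG is the target through which risk is to be reduced. If the intervention lowers GWG and lower GWG brings fewer complications, the complication carries information about the outcome. Holding it constant compares women who are alike in something that partly reflects their weight gain, which takes away part of the effect being estimated.

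The trial is planned with 80% power for a difference as large as 1.2 SD, so it has little power to spare. Its GWG results are also meant to inform the sample size of a larger trial, so a shrunken contrast would carry over into that design.

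**Working it through.** **1. The plan's own figure.** Inputs from Participants and Sample Size: 12 per group, standardized difference 1.2, two-sided 0.05. For a two-sample t test the degrees of freedom are 22, the critical value is 2.074 and the noncentrality is 1.2 × √(12/2) = 2.94. Power is 80.2%, which reproduces the stated 80%. The standard error of the difference is √(2/12) = 0.41 SD.

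**2. Adjusting when GWG itself is the response.** The documents give no complication rate and no odds ratio, so these are assumptions. GWG in SD units is Y = −1.2 × arm + N(0,1). The log odds of a complication are −1.1 + ln(OR) × (Y + 0.6), with OR per SD of GWG. The overall complication rate is then 26% to 32%. Y is regressed on arm and complication.

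The result can be checked by hand with the least-squares identity:

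adjusted effect = unadjusted effect − (complication coefficient) × (difference in complication rate, intervention minus control)

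| OR per SD | Rate, control / intervention | Coefficient | Adjusted effect | Shrinkage |
|---|---|---|---|---|
| 1.5 | 0.305 / 0.215 | 0.392 | −1.2 + 0.392 × 0.090 = −1.165 | 3% |
| 2 | 0.349 / 0.201 | 0.639 | −1.2 + 0.639 × 0.149 = −1.105 | 8% |
| 3 | 0.412 / 0.191 | 0.901 | −1.2 + 0.901 × 0.221 = −1.001 | 17% |
| 4 | 0.450 / 0.190 | 1.045 | −1.2 + 1.045 × 0.260 = −0.928 | 23% |

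The proportional shrinkage is the same for a true effect of 0.6 SD. If complications are unrelated to GWG (OR 1), it is zero.

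**3. Other assumed rates.** With a control rate of 35% and odds ratios of exp(0.5), exp(1.0) and exp(1.5), the shrinkage is 4.7%, 12.9% and 21.1%. With a control rate of 20% it is 2.5%, 8.8% and 14.0%.

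**4. Power at 12 per group.** Under the assumptions of step 2, simulated power falls from 80% to about 77% at an odds ratio of 1.5 and about 63% at 4. Separate runs differ by about a point. About two points of the loss would occur even with an unrelated covariate.

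**5. False positives.** If the intervention has no effect on GWG and does not act on complications by another route, the adjusted contrast is centred on zero and the type I error stays at about 5%. If the intervention lowers complications directly (assumed log odds −1.0, OR exp(1.0), 35% rate at mean control GWG) and has no effect on GWG, the adjusted contrast is shifted by +0.14 SD and the type I error is about 6.3%.

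**6. The pre/post mixed model.** In a balanced model with a random intercept, one pre and one post weight per woman and an arm-by-time effect, a covariate that is constant over time adds the same amount to both weights. It cancels from the change. In simulated data, adding an ever/never complication as a main effect left the arm-by-time estimate unchanged: −1.1038 with and without it at OR 2, and −1.1786 with and without it at OR 4. When the complication was time-varying or interacted with time, the estimates moved to about −1.00 and −0.85. These are shrinkages of 1 − 1.00/1.1038 = 9% and 1 − 0.85/1.1786 = 28% in those samples.

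The harm therefore depends on how the covariate enters the model, and the article does not state this.

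**The case against.** The strongest reply is that the sentence permits the harmful adjustment but does not prescribe it. Table 1 gives a preintervention value for complications, and that value would be a legitimate covariate. The adjustment is conditional, and in one natural form of the planned model it does nothing to the change contrast. All of this stands, and it limits how much can be claimed. It does not remove the point, because the article names the variable as a confounder without restricting it to the preintervention value, and most of its recording occasions come after randomisation.

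Several stronger readings are tempting but lack support:

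- **That the article says complications are caused by weight gain.** The Background says that GWG is related to them and predicts them. The phrase about targeting GWG to reduce risk leans toward a causal view, but the documents support only that complications may be consequences of the outcome.
- **That the conditional wording shows covariates will be chosen after the data are seen.** The full protocol and any analysis plan are not shown, and a covariate list is commonly fixed there. The same applies to gestational age at entry not being named. Unstratified randomisation of 30 women is a design choice and not an error.
- **That the adjustment would produce false positive findings.** When complications depend on arm only through GWG, the bias is toward zero and the type I error stays near 5%.
- **That the shrinkage is a property of this trial.** It rests on assumed odds ratios. Even the largest bias in the table, 0.27 SD, is below the standard error of 0.41 SD.

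Finally, the study is sized for feasibility and initial validation, and efficacy is left to a later trial. That lowers the stakes.

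**Conclusion.** The point holds in a limited form. The article puts obstetric complications among the confounders for the between-group models and does not confine them to values before randomisation. Complications that arise later do not confound the randomised contrast and, on the article's own rationale, may follow from the primary outcome.

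If they enter a model of GWG itself, the 1.2 SD effect shrinks by about 3% to 23%, and power falls from 80% to about 77% to 63%. This rests on assumed odds ratios of 1.5 to 4 per SD of GWG and complication rates of 26% to 32%, none of which the documents give. Attenuation also arises if they enter a pre/post model as a time-varying or time-interacted term. A time-invariant main effect in a balanced pre/post model leaves the change contrast unbiased.

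This should be fixed, because the correction costs almost nothing. It does not invalidate the trial.

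**What to change.** Replace the covariate sentence in Data Analysis with one to this effect: covariates in the between-group models are limited to variables measured before randomisation, such as prepregnancy weight or BMI and age; obstetric complications are used as a covariate only if already present at the preintervention assessment, or not at all; complications arising after randomisation are reported by arm.

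All these variables are already collected. The cost is one sentence and a few degrees of freedom for the baseline covariates that are kept.

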## Results

The targeted sample of pregnant women with overweight and obesity has been successfully recruited between January 13, 2016, and July 1, 2017. Baseline data have been collected for all participants. To date, 24 participants have completed the study and postintervention follow-up assessments, 3 are currently in progress, 1 dropped out, and 3 women had early miscarriages and are no longer active in the study.

## Discussion

### Principal Findings

To the best of our knowledge, this is the first study that is testing the feasibility of an individually tailored, adaptive intervention to manage GWG in pregnant women with overweight and obesity. This intervention, Healthy Mom Zone, aims to improve upon past interventions by addressing gaps in the literature, specifically among pregnant women with overweight and obesity, by providing a more individually tailored and adaptive approach to effectively manage weight gain during pregnancy. Although this intervention was deliberately intensive to understand if this approach can effectively manage GWG, future plans for this line of research will explore how the Healthy Mom Zone Intervention can be further adapted to women’s individual needs.

For example, we may learn from the study findings that some women can effectively manage their GWG with less intervention, and therefore, we can step down the intervention for them, whereas other women need the step up to keep their weight within their goals. This approach will also increase the clinical application and utility of the intervention.

### Strengths and Limitations

There are several positive features of this study. This study has strong public health relevance and clinical significance for the future management of GWG. We have also incorporated several innovative aspects into the study, including the use of (1) novel decision rules to choose when and how to adapt the intervention, (2) mHealth tools for self-monitoring of behaviors and real-time data collection to provide feedback to the participants, and (3) a unique computerized applet to generate individualized weight gain trajectories for comparing actual weight to the Institute of Medicine guidelines. In addition, customized eating and physical activity plans developed for this study aid in reducing participant barriers to engaging in healthy behaviors during pregnancy. Moreover, the intensive longitudinal data collection protocol allows for a myriad of systems approaches in support of implementing and evaluating intensively adaptive interventions [25,56-58]. Intensive data collection enables the application of system identification and state estimation approaches from engineering that, in turn, build comprehensive dynamical models for GWG used in adaptive intervention optimization. These methods can be used to estimate and correct energy intake over time, despite some missing data.

There are also some limitations of this research. The small sample size, although adequate for examination of the primary outcome (GWG), precludes the ability to make assumptions at a population level. Moreover, the target population is a homogenous sample of women from largely rural and suburban areas in Central Pennsylvania, thus limiting the extension of the study findings to more culturally diverse and urban populations of pregnant women with overweight and obesity. We do plan to understand the application of Healthy Mom Zone to a more diverse sample of pregnant women in the future, including those who are normal weight, more culturally diverse, and reside in varied communities across the United States.

